### Rescue therapy

In the event of a relapse, the patient will undergo appropriate investigations and be commenced on steroid therapy if appropriate. As these patients will then meet the McDonald 2010 criteria [31] for diagnosis of MS, they will be offered treatment in line with the current recommendations for first-line treatment of RRMS. They will be advised to continue study visits for the duration of the trial.

Participants with CIS whose MRI scans show new lesions at the end of the study period (24 weeks) meeting the McDonald 2010 criteria [31] for MS will also be offered first-line therapy for RRMS, as is standard practice in our institution.

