#### Inclusion criteria

1) Patients with CIS aged between 18 and 55 years will be eligible for entry into the study if symptom onset occurred within 3 months of screening, they have two or more asymptomatic T2 lesions on MRI brain consistent with demyelination, not treated with steroids within 30 days of screening and are not on any other DMT.

2) Healthy control participants will be recruited from hospital staff, and will be aged between 20 and 40 years with a female:male ratio of 2:1, in line with the gender ratio seen with CIS.

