#### Exclusion criteria

Exclusion criteria both for patients with CIS and for healthy control participants include: no history or evidence of hypercalcemia, renal impairment, vitamin D intolerance, parathyroid dysfunction, sarcoidosis, prior or current treatment with thiazide diuretics, or vitamin D supplementation of greater than 1,000 IU/day. Exclusion criteria for patients with CIS include: 1) if their symptoms might be explained by another diagnosis other than MS; 2) occurrence of an exacerbation less than 6 weeks prior to study entry; 3) previous treatment with β-interferons or glatiramer acetate in the 3 months before study entry, previous treatment with steroids in the 4 weeks before study entry, or any previous treatment with mitoxantrone or other immunosuppressant; and d) concurrent enrolment in any other clinical trial investigating DMT in CIS.

All female patients and healthy controls will be advised not to become pregnant for the duration of the study, and if sexually active to use effective contraception for the duration of the study and for 3 months after.

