### Statistical methods

All analyses assume a two-sided test of hypothesis with an overall α level of 0.05. Immunologic endpoints and *post hoc* analyses, which will include the 16 and 24 week endpoints, are considered exploratory, and will not be adjusted for multiple comparisons. Descriptive statistics will be presented as mean ± SD. Non-parametric tests will be used to compare characteristics between treatment groups. For outcomes, the sign/sign rank test will be used to evaluate continuous outcomes. McNemar testing will be used to categorize categorical and binary outcomes. For non-parametric testing on unpaired continuous data, the Wilcoxon rank sum test will be used. All outcomes will be adjusted for baseline serum 25(OH)D levels, and for mean serum levels achieved at weeks 16 and 24.

Missing data will be imputed as the mean of the preceding and following measurements. Only patients completing at least 4 months of full participation in the study or experiencing a relapse at any time in the study will be included in the final analysis. Non-adherent participants, defined as those with an increase in serum level of 25(OH)D of less than 50 nmol/l from baseline, will be excluded from the final analysis.

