In Ireland, the UK, Australia, and New Zealand, patients with CIS are treated conservatively until there is evidence, on clinical or MRI grounds, of dissemination in time. Patients with CIS form a distinct population with a well-established natural history, who are not exposed to immunomodulatory therapy. Given the standard practice in Ireland, there is no ethical concern with regard to watchful withholding of treatment. Should patients convert to RRMS during the trial, they will be offered standard DMT. This study should add to the growing evidence of the immunomodulatory effects of high-dose supplemental vitamin D in demyelinating disease. We hope to show that vitamin D is a safe and effective therapy for patients with CIS.

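### In the CIS group, immune values taken after relapse rescue stay in the only planned analysis, so vitamin D and rescue-drug effects cannot be separated; a pre-rescue analysis should be specified beside it

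*Protocol article*

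**What the plan says.** **Rescue therapy.** After a relapse, a CIS patient is investigated and will "be commenced on steroid therapy if appropriate". Such patients then meet the criteria for MS, so "they will be offered treatment in line with the current recommendations for first-line treatment of RRMS. They will be advised to continue study visits" until the trial ends.

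**Statistical methods.** The final analysis takes patients with at least 4 months of full participation "or experiencing a relapse at any time in the study will be included in the final analysis". Relapsers therefore enter by rule, even if they do not meet the 4-month condition. The stated adjustment is: "All outcomes will be adjusted for baseline serum 25(OH)D levels, and for mean serum levels achieved at weeks 16 and 24". Steroids and DMT do not appear in it. The same section removes participants whose vitamin D level rose too little: "Non-adherent participants, defined as those with an increase in serum level of 25(OH)D of less than 50 nmol/l from baseline, will be excluded".

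**Study endpoints and Figure 1.** The primary immune outcome is read at weeks 16 and 24 against baseline. MRI is done at baseline and week 24, in CIS patients only.

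**Inclusion and exclusion criteria.** At entry, CIS patients must be "not treated with steroids within 30 days of screening and are not on any other DMT". The exclusions also list "previous treatment with β-interferons or glatiramer acetate in the 3 months before study entry, previous treatment with steroids in the 4 weeks before study entry".

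**The concern.** The drug classes kept away from the baseline sample may be present at the two samples that define the primary endpoint. Suppose a placebo patient relapses at week 10, is given steroids and accepts DMT. That patient's cells at weeks 16 and 24 are analysed as placebo cells, although the IL-17, IFN-γ and IL-10 responses may have been changed by the rescue drugs.

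Rescue follows relapse, and relapse is an outcome the trial hopes vitamin D will reduce. If it does, rescue will be more common on placebo. If rescue drugs also move the immune measures in the same direction as vitamin D, the contrast between arms shrinks. If rescue is equally common in all arms, the between-arm bias is near zero, but the rescue effect still adds variance and still enters each arm's change from baseline. The arms are small enough for a few patients to matter.

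**Working it through.** **1. The plan's own group size.** For IL-17 after anti-CD3 stimulation, Sample size gives 44.5 ± 44.3, a standardised change of 44.5/44.3 = 1.005. A paired two-sided t-test at α = 0.05 has power 0.75 with n = 9 and 0.81 with n = 10, which reproduces the stated 10 per group. Allowing for dropout, 10/(1 − 0.30) = 14.3, rounded up to 15 per arm, or 45 CIS patients. With 30% dropout, 15 × 0.70 = 10.5 per arm remain.

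**2. How many could be rescued.** The document gives no 24-week relapse rate. For assumed rates p in an arm of 15:

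| p | Expected relapsers, 15p | Chance of at least one, 1 − (1 − p)^15 |
|---|---|---|
| 10% | 1.5 | 79% |
| 20% | 3.0 | 96% |
| 30% | 4.5 | 99.5% |

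These are upper limits for affected samples. Steroids are conditional, DMT is only offered, and a relapse after week 16 leaves the week-16 value untouched.

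**3. Bias in the arm contrast.** Bias = (difference between arms in the share rescued before sampling) × (rescue effect in SD). With an assumed difference of 0.1 to 0.3 and an assumed effect of 0.5 to 1.0 SD in vitamin D's direction, the bias runs from 0.1 × 0.5 = 0.05 SD to 0.3 × 1.0 = 0.30 SD. Against 1.005 SD, that is 5% to 30%.

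**4. Keeping or removing post-rescue samples.** This step uses the Th17 change and SD from Sample size, 1.9 and 1.8 (standardised 1.06). Let f be the share rescued before sampling, and let rescue shift the value by r × 1.9.

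- Remaining difference = 1.9 × [1 − r(f_placebo − f_active)].
- Variance per arm = 1.8² + f(1 − f)(1.9r)².
- Standardised effect = difference / √(mean of the two variances).

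Worked case: f = 0.3 on placebo, 0.1 on active, r = 1. Difference = 1.9 × 0.8 = 1.52. Variances = 3.24 + 0.21 × 3.61 = 4.00 and 3.24 + 0.09 × 3.61 = 3.56. Effect = 1.52/√3.78 = 0.78.

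Power is for a two-sided two-sample t-test at 0.05 (noncentral t), with 10.5 per arm when all samples are kept. Removing rescued patients leaves 10.5 × (1 − f) per arm: 7.35 at f = 0.3 and 9.45 at f = 0.1. The effect then returns to 1.06 if removal is harmless.

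| Rescued, placebo / active | r | Effect, all samples | Power, all samples | Power, pre-rescue only |
|---|---|---|---|---|
| 30% / 10% | 0.5 | 0.93 | 0.53 | 0.52 |
| 30% / 10% | 1 | 0.78 | 0.40 | 0.52 |
| 30% / 10% | 2 | 0.49 | 0.19 | 0.52 |
| 30% / 30% | 0.5 | 1.03 | 0.61 | 0.46 |
| 30% / 30% | 1 | 0.95 | 0.54 | 0.46 |
| 30% / 30% | 2 | 0.76 | 0.38 | 0.46 |

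The plan uses rank tests, so the t-test powers are approximations. The last column ignores any selection caused by removing patients because they relapsed. Neither handling is better throughout.

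**5. Which outcomes are exposed.** Week-16 and week-24 immune values in CIS patients are exposed when rescue came first. Week-24 MRI is exposed to a lesser degree, because new T2 lesions are counted against baseline and include those formed before rescue. The annualized relapse rate could change if rescue suppresses a second relapse. Time to first relapse and the relapse-free percentage are settled by the first relapse, before rescue. Healthy controls have no relapse rescue.

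**The case against.** **The SAP may deal with it.** The article condenses a fuller plan, and the handling of values after rescue is often left to the SAP. This stands in part: silence alone would be no finding. But the article does fix who is analysed and what is adjusted for. A SAP that merely followed it would keep these values with no term for rescue.

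**Analysing patients by assigned arm after rescue is legitimate.** It is, as a treatment-policy estimand. The article declares no such estimand, and excluding participants with a low 25(OH)D rise points the other way, towards the effect of vitamin D itself.

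**A reader might infer that post-rescue values should be removed from the main analysis.** The documents do not support that. Removal selects on relapse, which treatment may affect. At 30% rescue in both arms and r = 1 it lowers power from 0.54 to 0.46. A rescued patient would also lose the only follow-up scan. This objection stands, and it is why the pre-rescue analysis belongs beside the all-sample one.

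**A reader might infer that the Discussion contradicts Rescue therapy.** It says "Patients with CIS form a distinct population with a well-established natural history, who are not exposed to immunomodulatory therapy". The same paragraph adds that patients who convert during the trial will be offered standard DMT, so the two sections agree. The entry criteria are likewise washout periods before entry and place no ban on these drugs during the study.

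**A reader might infer that the vitamin D effect will be diluted.** That needs unequal rescue and a rescue effect in vitamin D's direction. The document supplies neither.

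**Conclusion.** The point holds as a weakness in the planned CIS immunologic analysis. Rescue therapy and Statistical methods together let rescue-drug effects into the week-16 and week-24 values, with nothing planned to separate them from vitamin D.

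Its size cannot be fixed from the document. The illustrated loss of 5% to 30% of the planned effect rests wholly on assumed rescue differences of 10 to 30 percentage points and assumed rescue effects of 0.5 to 1.0 SD in vitamin D's direction. With equal rescue the between-arm bias is near zero. With a rescue effect in the other direction the sign would reverse.

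The immunologic endpoints are declared exploratory, and the design is not invalidated. This is a specific, inexpensive improvement to one part of the primary endpoint, and it is credible only if settled before unblinding.

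**What to change.** Add to the statistical methods, before unblinding:

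1. All randomised CIS patients who relapse stay in follow-up and in the relapse and MRI endpoints.
2. The CIS immunologic comparison is reported twice: once with all samples, and once limited to samples taken before the first on-study steroid course or DMT. Values set aside in the second analysis are not refilled under the plan's rule of averaging neighbouring measurements, because the neighbour may itself be post-rescue.
3. Rescue use and timing are reported by arm.
4. Week-24 MRI results obtained after rescue are flagged and kept.

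The cost is a few sentences and slightly more analysis work. Medication changes are already recorded at every visit, so start dates should be obtainable from that record. The pre-rescue analysis will have fewer values, and it may be selected because relapse decides which values are removed. Showing both analyses lets the reader judge whether they agree. No change to rescue treatment is proposed.

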### Blinding

Patients, healthy control participants, and study staff, with the exception of the hospital pharmacist and internal monitor will remain blinded until the study database is locked at the end of the trial. The study drug (Vigantol®) and the placebo oil are identical in appearance, as is the labeling and packaging. Each bottle will have a unique four-digit product code, which has been generated by the hospital pharmacist, and ranges from 1000 to 2499. These numbers have been shuffled into random order, with the first group of 750 numbers assigned to the active product (Vigantol®**)** and the second group of 750 numbers to the placebo oil. Participants will be dispensed two identical bottles at 4-weekly intervals, which will be either two bottles of the study drug (Vigantol®), two bottles of placebo oil, or a bottle of each, equating to the two doses of vitamin D and placebo being investigated in this study. Participants will be advised to take a set dose from each bottle per day. Mechanisms are in place so that the code can be broken in the case of an emergency where it is essential for the clinical management of the subject.

### Sample size

The power calculations for this study were based on a pilot study, which examined immunologic outcomes in four healthy control participants treated with vitamin D 5,000 to 10,000 IU/day at our institution [32]. All calculations for numbers needed in the study were based on α = 5% and β = 80%. Based on flow cytometry analysis of T-cell subsets, the change in IL-17-producing CD4 T-cells (Th17 cells) had an effect size (mean ± SD) of 1.9 ± 1.8 indicating a need for five study subjects per group for 80% power. For IFN-γ-producing CD4 T-cells (Th1 cells), the effect size was 4.3 ± 6.3) indicating a need for 19 subjects per group for 80% power. The changes noted in cytokines in response to anti-CD3 stimulation of PBMC were 1) for IL-17, Δ = 44.5 ± 44.3, thus 10 participants needed in each group; 2) for IFN-γ, Δ = 32.8 ± 1.2, thus 6 needed in each group; and 3) for IL-10, Δ = −455 ± 27, thus number needed is < 5. The changes noted in cytokines in response to PPD stimulation were 1) for IFN-γ, Δ = 1860 ± 1835, thus 10 needed, in each group and 2) for IL-10, Δ = −576 ± 86, thus number needed is <5. On the basis of these results, at least 10 subjects should be included in each group (the only immunologic endpoint not powered would be the flow cytometry analysis of the IFN-γ-producing cells). Recruiting 39 healthy controls and 45 patients with CIS will allow for a drop-out rate of 20% and 30% respectively.

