### Study endpoints

The primary endpoint is the effect of oral vitamin D at 5,000 and 10,000 IU/day compared with placebo on the frequency of CD4 T-cell subsets and cytokine responses in peripheral blood mononuclear cells in patients with CIS and in healthy control participants at weeks 16 and 24 compared with baseline.

Secondary endpoints include: the following. 1) In the patients with CIS having MRI brain scans at baseline and week 24, the number of new and enlarging T2 lesions and gadolinium-enhancing lesions at week 24 compared with baseline in patients receiving oral vitamin D at 5000 IU and 10,000 IU/ day compared with placebo, 2) In the patients with CIS, the effects of oral vitamin D at 5,000 and 10,000 IU/day compared with placebo on relapse occurrence, calculated as the annualized relapse rate (ARR), the percentage of patients who are relapse-free, and time to first relapse. 3) The effects of oral vitamin D at 5,000 and 10,000 IU/day compared with placebo on the percentage of treated patients with CIS who are free from any evidence of disease (clinical and MRI) activity.

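### The 80% power figure comes from before-after changes pooled over dose in four healthy people; for the endpoints that set the sample size it is not shown for 5,000 IU, for CIS, or for a comparison with placebo

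*Protocol article*

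**What the plan says.** The Sample size section of the protocol article rests every power calculation on a pilot that "examined immunologic outcomes in four healthy control participants treated with vitamin D 5,000 to 10,000 IU/day". It reports seven changes, one mean and SD per immunologic endpoint, and splits none of them by dose. Each is turned into a number per group, for example "for IL-17, Δ = 44.5 ± 44.3, thus 10 participants needed in each group". The section concludes that "at least 10 subjects should be included in each group" and concedes that only the flow-cytometry IFN-γ (Th1) endpoint would then lack power. Allowing for drop-out, it arrives at 39 healthy controls and 45 patients with CIS, which is 13 and 15 per arm.

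The Study endpoints section defines the primary endpoint as "the effect of oral vitamin D at 5,000 and 10,000 IU/day compared with placebo", in CIS patients and in healthy controls. The title and the Trial design section present dose as a question of the study. The Discussion says that the best dose is unclear and that the trial has adequate power for its primary endpoint. The Trial design and Statistical methods sections call the trial and its immunologic endpoints exploratory.

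**The concern.** One pooled change per endpoint sizes two different dose arms. That treats the doses as equally effective, an assumption the article does not state and which the trial is partly meant to examine. If the effect rises with dose, the 5,000 IU effect lies below a pilot mean that includes higher doses. The pilot participants were healthy, yet the same number is carried to CIS without comment. The pilot description mentions no placebo group either, so its changes are before-after changes, while the endpoint is a difference from placebo.

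At stake is how a negative 5,000 IU result is read. With a general claim of adequate power in print, it could be taken as good evidence that the lower dose does nothing, when the comparison may have had little chance of detecting a smaller effect.

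**Working it through.** **Inputs.** From Sample size: "All calculations for numbers needed in the study were based on α = 5% and β = 80" per cent, read here as α = 5% and power 80%, with the means and SDs as printed. From Statistical methods: "All analyses assume a two-sided test of hypothesis with an overall α level of 0.05".

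**1. Reproducing the plan's figure.** Paired t-test with d = mean change / SD and noncentrality d·√n; power is the probability that the noncentral t on n − 1 df exceeds the two-sided 5% critical value.

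- IL-17, anti-CD3: d = 44.5/44.3 = 1.00. At n = 10, noncentrality is 3.18, critical value 2.262, power 81%. At n = 9 it is 75%. So 10, as stated.
- IFN-γ, PPD: d = 1860/1835 = 1.01, power 81% at n = 10. So 10, as stated.
- Th1: d = 4.3/6.3 = 0.68, giving 19, as stated ("the effect size was 4.3 ± 6.3) indicating a need for 19 subjects per group for 80% power").
- IL-10: |d| = 455/27 = 16.9 (anti-CD3) and 576/86 = 6.7 (PPD), giving 2 and 3, consistent with fewer than 5.
- Two figures do not reproduce: Th17 (d = 1.9/1.8 = 1.06) gives 10 against the stated "effect size (mean ± SD) of 1.9 ± 1.8 indicating a need for five study subjects per group for 80% power", and IFN-γ after anti-CD3 (d = 32.8/1.2 = 27.3) gives 2 against 6. Neither changes the overall 10.
- Drop-out: 10/0.8 = 12.5, so 13, times 3 = 39; 10/0.7 = 14.3, so 15, times 3 = 45.

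A two-sample t-test would need 17 per group for the endpoints stated as 10, so the plan's 10 is a within-arm, before-after number.

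**2. A smaller effect at 5,000 IU.** Let that effect be a fraction f of the pilot effect, SD unchanged; noncentrality becomes f·d·√n. The documents do not give f, so this is a range under assumption. Paired power for IL-17 after anti-CD3:

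| Completers per arm | f = 1 | f = 0.8 | f = 2/3 |
|---|---|---|---|
| 10 | 81% | 62% | 47% |
| 13 | 91% | 76% | 60% |
| 15 | 95% | 82% | 67% |

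At 10 completers and f = 0.8 or 2/3, IFN-γ after PPD gives 63% or 48%, and Th17 gives 66% or 51%. IL-17 keeps 80% only if f is at least about 0.99 (10 completers), 0.84 (13) or 0.78 (15). The three endpoints with |d| above 6 stay at about 100% even at f = 0.5.

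The chosen fractions follow if the effect is proportional to dose and each pilot participant took one of the two trial doses. With two of four on 5,000 IU the mean dose is 7,500 and f = 5,000/7,500 = 2/3. With three of four it is 6,250 and f = 0.80. The actual split is not reported.

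**3. Against placebo.** Two-sample t-test, noncentrality d/√(1/n₁ + 1/n₀), same SD in the placebo arm and no placebo change (both assumptions). For IL-17, 10 v 10 at the full pilot effect: 1.0045 × √5 = 2.25, critical value 2.101 on 18 df, power 57%. With no drop-out it is 69% (13 v 13) or 76% (15 v 15).

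Both vitamin D arms combined, 20 v 10: 1.0045 × √(20/3) = 2.59, critical value 2.048 on 28 df, power 71%. Under dose-proportionality with the 2:2 split, the arms have 2/3 and 4/3 of the pilot effect: 29% for 5,000 IU, 81% for 10,000 IU, and 68% combined (by simulation).

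The article names rank tests; the t-test figures are used because they reproduce its own numbers.

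**The case against.** A reader might infer that the 80% claim cannot hold for the lower dose. The documents do not support that. There are seven pooled effects, not one; three keep nearly full power at half the effect, and Th1 is already conceded. A dose-ranging design asks whether effects differ by dose; it does not assert that they do. The stated rationale is closer to a threshold. The Background and Discussion look for serum levels above 100 nmol/l and present 5,000 to 10,000 IU/day as enough to reach them. The Background gives a winter mean of 36.4 nmol/l in healthy Irish controls and a rise of 150 nmol/l on 10,000 IU. If half the dose gives half the rise (assumption), 5,000 IU leads to 36.4 + 75 = 111.4 nmol/l. Similar effects at both doses are therefore compatible with the document, and the shortfall in step 2 would then disappear. Ten completers is also the worst case the plan allows.

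A reader might also infer that combined vitamin D against placebo is the contrast the pilot supports and should come first. It is not: four treated people with no described placebo group support a before-after change. Under proportionality, the combined contrast (68%) is weaker than 10,000 IU alone (81%). Nor can one say that a combined analysis is absent from the trial, since a journal article condenses the full protocol.

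The exploratory label limits the harm. It does not remove the point, because the article claims adequate power without saying which dose, population or comparison the claim covers.

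**Conclusion.** The point holds as a limit on what has been shown. For IL-17 after anti-CD3, IFN-γ after PPD and Th17, 80% power at 10 per group is a before-after figure for mixed doses in healthy people, and it is not shown for 5,000 IU or for CIS. The first two have almost no reserve at 10 completers. The size of any loss at 5,000 IU depends on an unreported dose split, an unknown dose-response and a constant SD, and it may be nil.

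The gap against placebo is separate and does not depend on the dose-response: about 57% for IL-17 at 10 v 10 with the full pilot effect, given the same SD and no placebo change. This is a matter of wording and a modest addition to the analysis. It does not make the design invalid.

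**What to change.** In Sample size, state that the figure is a before-after calculation for mixed doses of 5,000 to 10,000 IU/day in healthy people. Give power for each dose against placebo over a stated range of dose effects, at 10 completers and at full enrolment, and mark the CIS figure as extrapolated. In the Discussion, qualify the claim of adequate power accordingly.

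Within each population, add both vitamin D arms combined against placebo as a supplementary exploratory contrast, beside the dose-specific comparisons and not ahead of them. At 20 v 10 it has 71% power for IL-17 if the doses act equally and 68% if effects are dose-proportional, against 57% and 29% for 5,000 IU alone.

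The cost is some wording and one analysis of data already collected. The drawbacks are one more unadjusted comparison and an estimate that does not speak to a single dose.

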## Discussion

Supplemental vitamin D appears to have potential as a therapeutic agent for MS; what is less clear is the optimal dose of vitamin D needed to effect change within the immune system. Our study is designed to address this question, and to add to the growing evidence of the safety and tolerability of high-dose vitamin D supplementation. As this is a phase II randomized, placebo-controlled trial with two distinct study groups and is adequately powered to meet the primary endpoint, it should be considered a high-quality trial aiming to provide class II evidence of the primary endpoint.

Existing guidelines on vitamin D supplementation are conservative, and refer mainly to bone health [33], with 4,000 IU considered the upper limit of tolerability, despite the fact that sun exposure can provide an adult with up to 20,000 IU per day [34]. Older adults are now advised to sustain 25(OH) D concentrations of greater than 75 nmol/l for optimal bone health and, in order to achieve that, they need to consume approximately 4,000 IU/day of vitamin D [18,35]. Levels greater than 100 nmol/l are needed to ensure that patients are receiving adequate immunomodulating doses of vitamin D. Based on previous dosing studies [18], the maximum serum 25(OH)D level expected with a daily dose of 10,000 IU is approximately 250 nmol/l, making both treatment doses safe and tolerable.

The availability of DMT and the earlier recognition and diagnosis of MS have a significant effect on trial design for the evaluation of new drugs, and this also raises ethical concerns. Most would feel that placebo-controlled studies of the RRMS population are unethical. This results in the need for large multicenter trials to achieve adequate numbers to power the study over longer time periods to assess for clinical endpoints. Thus, costs are generally prohibitive and really limits these studies to large pharmaceutical companies.

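### The sample size is computed for a within-person change in one treated group, so 80% power against placebo, which is the primary comparison, is not shown at 10 per arm

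*Protocol article*

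**What the plan says.** Under Study endpoints, the contrast is with placebo: "The primary endpoint is the effect of oral vitamin D at 5,000 and 10,000 IU/day compared with placebo", for T-cell subset frequencies and cytokine responses, in patients and in healthy controls. Under Randomization, the two populations are allocated separately to three equal arms.

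Under Sample size, the inputs are changes observed in "four healthy control participants treated with vitamin D 5,000 to 10,000 IU/day at our institution". No placebo group is mentioned. Each measure has a mean change, an SD and a number needed:

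- Th17 cells: "effect size (mean ± SD) of 1.9 ± 1.8 indicating a need for five study subjects per group for 80% power".
- Th1 cells: 4.3 ± 6.3, 19 per group.
- Anti-CD3 stimulation: IL-17 44.5 ± 44.3, 10 per group; "for IFN-γ, Δ = 32.8 ± 1.2, thus 6 needed in each group"; IL-10 −455 ± 27, fewer than 5.
- PPD stimulation: IFN-γ 1860 ± 1835, 10 per group; IL-10 −576 ± 86, fewer than 5.

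The section concludes "On the basis of these results, at least 10 subjects should be included in each group" and names Th1 flow cytometry as the single immunologic measure without adequate power. The Discussion says the trial "is adequately powered to meet the primary endpoint" and, partly on that ground, describes it as a high-quality trial aiming at class II evidence.

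**The concern.** A change from baseline in one treated group and a difference in change between a treated arm and placebo are different quantities. The second carries the sampling error of two arms. A size that gives 80% power for the first gives clearly less for the second, unless placebo changes hardly vary at all.

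What is at stake is how the placebo comparison will be read. The power statement tells a reader how much weight a null difference can bear, and the Discussion leans on it when grading the evidence. There is also an internal conflict. Th1 frequency is one of the CD4 subset measures in the primary endpoint and is conceded to lack power, yet the Discussion claims adequate power for the primary endpoint without qualification.

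**Working it through.** **Inputs.** Means, SDs and stated n are from Sample size. The two-sided 5% level is from Statistical methods ("All analyses assume a two-sided test of hypothesis with an overall α level of 0.05"). Power is taken as 80%: Sample size prints that figure as β but elsewhere calls it power. Planned evaluable numbers are 39/3 × 0.8 = 10.4 per arm for controls and 45/3 × 0.7 = 10.5 per arm for patients, so the stated drop-out allowances do lead to 10 per arm.

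**Formulas.** With d = mean/SD:

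- Paired (one-sample) t: noncentrality d√n, n − 1 degrees of freedom.
- Two-sample t, n per arm: noncentrality d√(n/2), 2n − 2 degrees of freedom.

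**Reproducing the plan.** For anti-CD3 IL-17, d = 44.5/44.3 = 1.005. Paired with n = 10, the noncentrality is 1.005 × √10 = 3.18 and power is 80.7%; with n = 9 it is 75.2%. So n = 10, as stated. PPD IFN-γ (10) and Th1 (19) reproduce in the same way. The alternatives do not give 10, 10 and 19: two-sample t gives 17, 17 and 35; two-sample normal approximation 16, 16 and 34; one-sided two-sample t 13, 13 and 28; one-sample normal approximation 8, 8 and 17.

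**Power against placebo.** Assume that the placebo mean change is zero, the SD of change is the same in both arms, and the pilot mean is the true difference. For IL-17 at 10 per arm, the noncentrality is 1.005 × √5 = 2.25 and power is 56.6%. Rank-sum power, for the test that Statistical methods names for unpaired data, was simulated with normal data (at least 20,000 replicates).

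| Measure | d | Stated n | Paired n (power) | Two-sample n per arm | Power vs placebo at 10 per arm, rank-sum to t |
|---|---|---|---|---|---|
| Anti-CD3 IL-17 | 1.005 | 10 | 10 (80.7%) | 17 | 51%-57% |
| PPD IFN-γ | 1.014 | 10 | 10 (81.3%) | 17 | 52%-57% |
| Th1 | 0.683 | 19 | 19 (80.3%) | 35 | 27%-30% |
| Th17 | 1.056 | 5 | 10 (84.3%) | 16 | 56%-61% |

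The difference detectable with 80% power at 10 per arm is about 1.3 SD (two-sample t).

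**Sensitivity.** With the placebo SD halved, simulated power is about 71%-78% for IL-17 and PPD IFN-γ. With equal SDs and no drop-out at all, two-sample t power for these two is 69%-70% at 13 per arm and 76% at 15.

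**Measures that stay powered.** As printed, d is 32.8/1.2 = 27.3 for anti-CD3 IFN-γ, 455/27 = 16.9 for anti-CD3 IL-10 and 576/86 = 6.7 for PPD IL-10. Any of the tests has ample power for these at 10 per arm.

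**Two entries that do not fit.**

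- *Th17, n = 5.* Paired t power with 5 subjects is 44%. A two-sided sign or signed-rank test cannot reach 5% with 5, since its smallest p is 2/2⁵ = 0.0625. The paired t size is 10.
- *Anti-CD3 IFN-γ, n = 6.* With d = 27.3, the paired t size is 2. Six is the smallest n at which a two-sided sign or signed-rank test can reach 5% (2/2⁶ = 0.031), so that may be its origin. The same rule would forbid the figure below 5 given for IL-10.

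**The case against.** The strongest reply is that the calculation fits part of the analysis. Statistical methods lists sign and signed-rank tests for continuous outcomes, and at 10 subjects the signed-rank test has about 80% power for IL-17 and PPD IFN-γ within an arm. The trial is called exploratory, and the Th1 shortfall is disclosed. All of that is true. It explains where the 10 came from, but a within-arm test does not address the placebo contrast in Study endpoints, and an exploratory label does not make a stated power correct.

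Four stronger readings are tempting and should be resisted.

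- *That true power is 51%-57%.* The pilot had four people. A 95% interval for an SD from four normal observations runs from 0.57 to 3.7 times the estimate; with the mean change held fixed, two-sample t power for IL-17 would then run from about 96% down to 9%. The placebo SD is unknown. The figures show what the plan's own inputs imply under a stated assumption.
- *That 61% belongs to the measures that set the sample size.* It is the Th17 figure, and the article says Th17 needs only five.
- *That the whole primary endpoint lacks power.* Three of the seven listed measures keep it, as printed.
- *That the printed IFN-γ SD is wrong.* The sign-test route could give six. The entries are inconsistent in method, and the pilot data that would settle the matter are not in the article.

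Nor does the article say how a null result will be interpreted, so over-reading is a risk and not a stated intention.

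**Conclusion.** The point holds. The sample size is for within-person change in one treated group, while the primary endpoint is a comparison with placebo, so 80% power for that comparison is not shown. On the plan's own inputs, with zero mean change and equal SD in placebo, the shortfall for the two measures that set the 10 is 23 to 29 percentage points (80 minus 57 and 80 minus 51). Halving the placebo SD narrows it to about 2 to 9 points without closing it. A placebo change in the same direction as the active arms would widen it.

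The Th17 number of 5 is wrong for the printed mean and SD under either paired method. The IFN-γ number of 6 needs checking. The statement that only Th1 lacks power fails for the placebo contrast under these assumptions. The Discussion's unqualified claim also conflicts with the article's own Th1 concession, before any recalculation.

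**What to change.** 1. In Sample size, state that the calculation is for change within one treated arm.
2. Add power against placebo at 10 evaluable per arm: about 50%-60% for anti-CD3 IL-17, PPD IFN-γ and Th17, about 30% for Th1, with a detectable difference of about 1.3 SD. Give the zero-change and equal-SD assumptions, and the range if the placebo SD differs. Say which measures remain powered.
3. Correct the Th17 entry to 10 paired, or 16 per arm against placebo. Check the SD and the method behind the anti-CD3 IFN-γ entry, and use one method throughout.
4. Delete the statement that Th1 is the only measure without power, and in the Discussion the claim that the trial "is adequately powered to meet the primary endpoint".

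The cost is less favourable stated figures; recruitment and allocation are unchanged.

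An analysis pooling patients and controls, stratified by population, could be added as optional support. It is not part of this correction: the two groups are randomized and sized separately, pooling assumes similar effects in both, and an interaction check with 10 per cell would have little power to test that.
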